#### Symptoms of depression

The low mood subscale of the German translation [101] of the Revised Children’s Anxiety and Depression Scale (R-CADS) [80] will be used to assess whether children display depressive symptomology, since both IB and cortisol reactivity may be influenced by symptoms of depression. The R-CADS [80] is a 47-item self-report questionnaire with response options depicted on a 4-point Likert scale. The R-CADS [80] is made up of six subscales. The German version of the depression subscale was found to have good internal consistency (Cronbach’s α = 0.87) [101]. And was strongly associated with the Depression Inventory for Children and Adolescents (DIKJ), *r* = 0.78, showing good convergent validity [101].

#### Symptoms of anxiety

The sum of the five anxiety subscales of the German translation [101] of the Revised Children’s Anxiety and Depression Stress Scale (R-CADS) [80] will be used to assess whether children display symptoms of anxiety, since both IB and cortisol reactivity may be influenced by symptoms of anxiety. The anxiety subscales of the German version of the R-CADS [80] were found to have good internal consistency (Cronbach’s α = 0.94) [101]. The relationship between the German version of the R-CADS [80] anxiety subscales and the Anxiety Questionnaire for Pupils (AFS) [102] and the total score of the Spence Children's Anxiety Scale (SCAS) [103] was found to be strong, *r* = 0.81 and *r* = 0.94 respectively, showing good convergent validity [101].

#### Childhood trauma

The German version [104] of the Childhood Trauma Questionnaire (CTQ) [77] will be used to assess whether participants have experienced trauma, since childhood trauma has previously been found to be associated with distinct salivary cortisol patterns [105]. The CTQ [77] is a 28-item self-report questionnaire assessing retrospective episodes of physical, sexual, and emotional abuse. The psychometric properties of the CTQ [77] have been assessed in both clinical [106, 107] and community samples and were found to be good [108].

### Statistical analyses

#### Cortisol data analyses

Stress reactivity and recovery will be measured via cortisol obtained from saliva swabs pre (T1) and post (T2) the IB intervention. During each assessment session (T1 and T2), cortisol will be sampled at six timepoints; Pre-TSST-C [82], immediately post, 10 min post, 20 min post, 30 min post and 45 min post-TSST-C [82]. The baseline cortisol measurement (pre TSST-C [82]) will be taken after a 30-min acclimation period. This is necessary so that the initial cortisol measurement is reflective of basal cortisol, rather than the stress response associated with part-taking in an experiment in an unfamiliar laboratory setting [18]. Testing will take place between 2 and 7 pm to maximize feasibility by having a reasonable time window and minimise the time of the day effect which is evident in cortisol studies [109].

#### Cortisol data preparation

First, we will check the distributional characteristics of the baseline cortisol data (i.e., cortisol levels pre-TSST-C at session 1). It is expected that some participants will have high baseline cortisol concentrations and that these participants will be unable to elicit a cortisol response to the laboratory stressor (suppression of HPA axis response due to negative feedback [110]). Without knowing the distribution of cortisol values, it is difficult to determine a numerical cut-off. Therefore, we plan to exclude participants whose baseline cortisol levels are significantly higher from other cases in the distribution. We will transform the remaining cortisol data into standardized values (z-scores) and check for outliers by inspecting the respective histograms for each cortisol variable. We will consider z-scores above + 3.29 or below -3.29 as outliers. Once outliers are removed, we will determine the normality of all cortisol variables using the Shapiro–Wilk-Test. If more than one cortisol variable fails the test for normality, all cortisol values will be log transformed before further analyses are conducted.

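### The 3.29 SD outlier screen is applied to untransformed cortisol before the log transform, so it removes genuine strong responders; the high-baseline exclusion has no fixed cut-off

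*Protocol article*

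**What the plan says.** The Cortisol data preparation section of the protocol article sets out four steps in order.

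1. Look at the session-1 pre-stressor values and drop high baselines: "we plan to exclude participants whose baseline cortisol levels are significantly higher from other cases in the distribution". No number is given, because "Without knowing the distribution of cortisol values, it is difficult to determine a numerical cut-off". The reason offered is physiological: "these participants will be unable to elicit a cortisol response to the laboratory stressor".
2. Standardise and screen what is left: "We will transform the remaining cortisol data into standardized values (z-scores) and check for outliers by inspecting the respective histograms for each cortisol variable". The limit follows: "We will consider z-scores above + 3.29 or below -3.29 as outliers".
3. Test normality on the screened data: "Once outliers are removed, we will determine the normality of all cortisol variables using the Shapiro–Wilk-Test".
4. Transform conditionally: "If more than one cortisol variable fails the test for normality, all cortisol values will be log transformed before further analyses are conducted".

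The Cortisol data analyses section shows how many variables this covers: "During each assessment session (T1 and T2), cortisol will be sampled at six timepoints", which is 6 x 2 = 12 for each high-risk child. Under Computation of response indices, reactivity is the difference between baseline and peak, and recovery is the 45-minute value corrected for baseline. The article does not say whether an outlying value or the whole child is removed.

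**The concern.** A limit of 3.29 standard deviations is a sensible screen when values are roughly normal. The plan itself allows for skew: it expects some high baselines and keeps a log transform in reserve. Screening before that transform treats the ordinary upper tail of a skewed variable as error, and a child with a large post-stressor rise is in that tail. Reactivity and recovery are primary outcomes, so the values most at risk are those the trial is meant to measure.

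Two further features matter. The screen also runs on T2 samples, which are post-randomisation outcomes. If the intervention lowers cortisol, more placebo than active children will cross the limit. The high-baseline exclusion is a different kind of problem: it is a judgement made after seeing the data, with no criterion fixed in advance.

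**Working it through.** **Inputs.** From the article: limit 3.29; 12 cortisol variables per child; 100 high-risk children, 50 per arm; order of steps as above. Not in the article, so assumed: lognormal cortisol with log-SD 0.3 to 0.8, and the correlations given below. The screen is taken to run over the 100 high-risk children.

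**Nominal rate of the rule.** For normal data, P(|z| > 3.29) = 0.0010, or 0.10% of values.

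**Rate on untransformed skewed data.** Take a lognormal variable with median 1 and log-SD s. Its mean is m = exp(s²/2), its SD is d = m·√(exp(s²) − 1), and the limits are m ± 3.29d.

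| s | m | d | upper limit | upper limit in log-SDs | share above | lower limit |
|---|---|---|---|---|---|---|
| 0.3 | 1.046 | 0.321 | 2.10 | 2.48 | 0.66% | −0.01 |
| 0.5 | 1.133 | 0.604 | 3.12 | 2.28 | 1.14% | −0.85 |
| 0.8 | 1.377 | 1.304 | 5.67 | 2.17 | 1.51% | −2.91 |

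The rule flags about 7 to 15 times its nominal share (0.66/0.10 to 1.51/0.10). The lower limit is below zero throughout, so no low value can be flagged.

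**Who is flagged.** First simulation: 100 children x 12 samples, median two-fold peak rise, baseline log-SD 0.3-0.7, response log-SD 0.3-0.5, noise log-SD 0.2. Untransformed screening flags 4.3-5.0 children per 100; log-scale screening flags 0.3-0.5. Of the top tenth by T1 reactivity, 32-37% have a flagged value, against 1-2% of the other children. That is 3.2 to 3.7 of the 4.3 to 5.0 flagged children, so most of those flagged are strong responders. Every simulated value was genuine.

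**Effect on the comparison.** Second simulation: 12 lognormal samples, correlation 0.75 within and 0.5 between sessions. With no treatment effect, 5.2%, 7.6% and 9.2% of children are flagged at log-SD 0.4, 0.6 and 0.8, against 0.6% on the log scale; at log-SD 0.3 the share is about 4%. Now add a true 0.3 log-unit reduction at T2 in the active arm and drop the flagged children:

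| log-SD | placebo flagged | active flagged | untransformed delta difference, before → after | shrinkage |
|---|---|---|---|---|
| 0.4 | 6.9% | 3.8% | 0.684 → 0.610 | 1 − 0.610/0.684 = 11% |
| 0.6 | 9.2% | 6.2% | 0.808 → 0.650 | 1 − 0.650/0.808 = 20% |
| 0.8 | 10.6% | 7.9% | 1.029 → 0.737 | 1 − 0.737/1.029 = 28% |

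Across log-SD 0.3-0.8, 20-48% of the top tenth by T2 reactivity are flagged.

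**Which scale the plan would use.** After the screen, more than one variable fails Shapiro-Wilk in 100% of runs at log-SD 0.4-0.8, and in at least 99.5% at 0.3. The plan then logs everything. On that scale the arm difference shrinks by only about 1-2.5%. At log-SD 0.8, power for log reactivity is about 81% with the untransformed screen and 86% with the log-scale screen. At smaller log-SDs, power for this assumed effect is close to its ceiling, so the comparison shows little there.

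**The case against.** The strongest reply is that the conditional log transform does its job. A reader of the table above might infer that the plan understates a true effect by 11-28%. The article does not support that: those figures are for an untransformed delta, and under the skew that produces them the plan's own normality test sends the analysis to the log scale. Trimming the tail first does make Shapiro-Wilk less likely to fail, but in these settings hardly ever enough to change the outcome. This part of the objection stands in full. With no treatment effect, the screen also creates no bias between arms.

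A reader might also infer that the high-baseline exclusion deletes large responders or favours an arm. It targets children whom the plan expects not to respond, and it uses a value taken before randomisation. Outcome assessors know the allocation, but the article does not say who sets the cut-off or whether that person sees the arm. Whether such children belong in the primary analysis is a debatable trade-off, since the plan gives a physiological reason for leaving them out.

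It might be inferred, too, that a deleted peak lets a lower sample stand in as the peak. That holds only if single values are removed, which the text leaves open.

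Finally, the sample size has some slack: 70/(1 − 0.20) = 87.5, rounded to 88, then raised to 100, which leaves 12 children. That exceeds the number flagged here, although the baseline exclusion and the exclusion of children completing less than 80% of the training can draw on the same margin.

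None of this justifies the order of steps. The children lost are genuine responders, and the loss is avoidable.

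**Conclusion.** The point holds in a limited form. The order of steps is stated in the article and is wrong for skewed data: it removes only high values, mostly from strong responders, at about 4-9% of children instead of about 0.6%. Removal at T2 depends on outcome and is unequal between arms when the treatment works. On the log-scale analysis the plan would almost certainly reach, bias in the arm contrast is small (about 1-2.5%). The practical cost is lost participants and some power, about five percentage points in the most skewed setting examined.

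The sizes rest on an assumed lognormal shape, assumed spreads and correlations, an assumed 0.3 log-unit effect and removal of whole children; the article gives no cortisol variance. The direction needs only right skew.

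The fault in the high-baseline exclusion is discretion: the criterion is undefined and is chosen after the data are seen. It should be corrected, but it is a separate and lesser matter.

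**What to change.** - Log-transform all cortisol values at the outset, whatever Shapiro-Wilk would show.
- Apply the 3.29 screen to the logged values, and state whether a flagged value or the whole child is removed.
- Write down the high-baseline exclusion rule before the comparison is run, setting it on data with arm labels removed.
- Report a sensitivity analysis of reactivity and recovery with every value kept.

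The cost is analysis wording only, with no change to sampling or sample size. The one downside is interpretive: reactivity becomes a log difference, read as a ratio of peak to baseline instead of an absolute rise. The plan already accepts that reading whenever its conditional transform applies.

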#### Computation of response indices

We will first compute response indices for both TSST-Cs (pre and post intervention) according to the following procedures: Stress reactivity will be calculated via delta cortisol (i.e., the maximum cortisol increase) by subtracting peak cortisol values (measured either at + 1, + 10, + 20 or + 30 min post-TSST-C) from baseline cortisol values (cortisol measured at -1 min relative to the TSST-C). This has been shown to be a more direct measure of stress reactivity [48] compared to other techniques such as the commonly used AUC method [50]. Stress recovery will be analysed via the salivary cortisol swab taken at 45 min post stressor, correcting for baseline cortisol. The somewhat more intuitive measure of recovery (delta between peak and 45 min post stress) would likely be highly correlated with and driven by cortisol reactivity [111].

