#### Hypothesis testing

To test the hypotheses that HR children have more negative IB (H1) and altered cortisol reactivity and recovery (H2, H3) when compared with LR children at T1, t-tests will be performed using IB, cortisol reactivity and recovery as dependant variables (DVs) and group membership (HR, LR) as the independent variable (IV). No specific predictions about the direction of effects for participants’ cortisol reactivity (H2) are made given the mixed literature [18]. For cortisol recovery (H3), it is predicted that HR participants’ cortisol levels will take longer to return to baseline after experiencing the laboratory stressor [47, 111]. Furthermore, to account for the possible confounding variables assessed in this study, a regression model will be run for the effect of group on IB, including age, depression and anxiety symptoms, childhood trauma, sex and pubertal status as covariates. The association between baseline IB and stress response will be looked at within each group (HR and LR) as well as in the entire sample using bivariate correlation. Bayes Factors will be calculated to warrant a rejection of the null hypothesis.

To determine whether the IB training was indeed more effective than the placebo training (H4) in HR individuals, a manipulation check will be conducted using ANOVA. In line with a previous study, participants who complete less than 80% of the training will be excluded from analyses [85].

To test the hypothesis, that the active (versus placebo) IB condition exerts effects on HR individuals’ stress reactivity and recovery (H5 and H6), an ANOVA will be conducted with the condition as the IV (active vs. placebo IB intervention) and cortisol reactivity and recovery as the DVs. Exploratory analyses will be conducted to determine the relationship between change in IB and change in stress response in HR individuals. All relevant confounding variables assessed in this study will be accounted for (age, symptoms of depression and anxiety, childhood trauma, sex, pubertal status, baseline cortisol response). Additionally, Bayes Factors will be calculated to determine whether the null hypothesis can be rejected.

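### A count of normality-test failures decides whether primary cortisol reactivity is an absolute increase or a fold change, and only the increase is defined

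*Protocol article*

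**What the plan says.** All places are in the protocol article, under Statistical analyses unless noted.

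- **Cortisol data preparation** first removes outliers ("We will consider z-scores above + 3.29 or below -3.29 as outliers"). Next, "we will determine the normality of all cortisol variables using the Shapiro–Wilk-Test". The consequence follows: "If more than one cortisol variable fails the test for normality, all cortisol values will be log transformed before further analyses are conducted". The level of the test and the set of variables counted are not given.
- **Cortisol data analyses**: "During each assessment session (T1 and T2), cortisol will be sampled at six timepoints". The count could therefore run over 6 variables (one session) or 12 (both).
- **Computation of response indices** comes after the log step: "Stress reactivity will be calculated via delta cortisol (i.e., the maximum cortisol increase) by subtracting peak cortisol values". For recovery: "Stress recovery will be analysed via the salivary cortisol swab taken at 45 min post stressor, correcting for baseline cortisol". Neither index has a second definition or interpretation for logged values.
- **Outcome measures** (under Measures) makes reactivity and recovery primary, next to interpretation bias.
- **Hypothesis testing** uses t-tests for high-risk (HR) versus low-risk (LR) children (H2, H3) and ANOVA for active versus placebo (H5, H6). For H2 the article states: "No specific predictions about the direction of effects for" cortisol reactivity.

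**The concern.** There are two separate problems.

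1. **The estimand is conditional.** The log step precedes the subtraction. If it is triggered, reactivity is a relative rise; if not, it is an absolute rise. These are different questions, and the text names and interprets only an increase. The rule fixes in advance how the switch works, but not which question the primary outcome answers.
2. **The trigger looks at the wrong quantities.** The t-tests and ANOVA rely on the residuals of the analysed indices. The rule tests the marginal distributions of separate swab values. LR children give samples at T1, and the text does not say whether they enter the count, so non-randomised children could influence the scale used in the randomised comparison.

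At stake is whether a reader can tell what a reactivity result means, and whether the result would have been the same on the other scale. H2 is undirected, and the Background states the RCT hypothesis only as an altered response. A sign that depended on the scale would therefore not stand out as unexpected.

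**Working it through.** **1. The plan's own figure.** Sample size gives N = 70 from g = 0.34, α = 0.05, power 0.80, two groups and two time points. With f = g/2 = 0.17 and an assumed pre-post correlation of 0.5, λ = N·f²·m/(1−ρ) = 70 × 0.0289 × 2/0.5 = 8.09, and power is 0.8007. N = 70 is reproduced, and 70/0.8 = 87.5 gives the stated 88. The point here does not affect these figures or the target of 100.

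**2. What the subtraction means.** Take delta as peak minus pre-stressor value, since the text calls it an increase. With pre-stressor level B and fold rise F = peak/B:

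- raw delta = B·F − B = B(F − 1)
- log delta = ln(B·F) − ln(B) = ln(F)

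The choice of peak sample is unaffected, because the log is monotone. At a fixed B both deltas rise with the peak, so they rank two children or groups differently only when B differs. With illustrative values:

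| | Pre-stressor | Peak | Raw delta | Fold | Log delta |
|---|---|---|---|---|---|
| Active | 4 | 10 | +6 | 2.50 | 0.916 |
| Placebo | 6 | 13 | +7 | 2.17 | 0.773 |

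The raw scale calls placebo more reactive; the log scale calls active more reactive.

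**3. How often the switch fires.** The document gives no cortisol SD or correlation and no test level. Level 0.05 is assumed, and SDs are shown as ranges.

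- Truly normal, independent variables: P(at least 2 failures) = 1 − 0.95^k − k × 0.05 × 0.95^(k−1). This is 3.3% for k = 6 and 11.8% for k = 12. With correlated variables, simulation gives 2–3% and 8–9%.
- Lognormal data after the ±3.29 rule:

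| Log-SD | n = 70, 6 var. | n = 70, 12 var. | n = 100, 6 var. | n = 100, 12 var. |
|---|---|---|---|---|
| 0.10 | 14% | 32% | 18% | 40% |
| 0.15 | 29% | 60% | 40% | 78% |
| 0.20 | 52% | 87% | 73% | 94% |

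At log-SD 0.4 or more the switch fires in at least 99.7%. With milder skew, whether 6 or 12 variables are counted changes the outcome materially.

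**4. How often the scales disagree in the RCT** (simulated). With 50 per arm and log-SDs of 0.3 to 0.6:

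- No true effect: significance differs in 5–6% of trials.
- Fold rise 14% lower, equal pre-stressor levels: significance differs in 15–26%, estimated direction in 2–13%.
- Pre-stressor level 22% lower, same fold rise: raw rejects in 13–43%, log in about 5%.
- Significant results in opposite directions: 0.12% or less in every scenario.

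At these SDs the log branch is close to certain, so these rates show that the scale matters, not that the rule wavers. For both together: with 40 per arm, 12 variables, log-SD 0.15 to 0.25 and a 10% smaller rise, the switch fired in 50–84% of trials and the scales disagreed on significance in 21–32%.

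**5. HR versus LR (H2).** Assumed: basal mean 4, log-SD 0.5; additive rise with mean 5, log-SD 0.6; 15% sample noise; HR n = 100; LR n not stated, 100 assumed.

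| HR relative to LR | Raw | Log |
|---|---|---|
| Basal +20%, same absolute rise | rejects 5% | rejects 27%, d = −0.20 |
| Basal +20%, same fold rise | rejects 42%, d = +0.25 | rejects 4% |
| Basal +25%, rise +10% | d = +0.12 | d = −0.15 |

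**The case against.** The strongest reply is that the uncertainty and the harm seldom occur together. At log-SD 0.5 to 0.6 the log branch ran in every simulated trial, so the rule's verdict did not depend on chance. At log-SD 0.15 the switch was uncertain (46–60%), but for a 20% smaller rise the scales disagreed in only 2% of trials, and for a 40% smaller rise in none. This largely stands for large effects and for strong skew. It does not stand for a small effect with mild skew, where section 4 of the working shows both at once. With strong skew the mismatch with the written definition remains.

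A second reply is that the article never says absolute; read in order, delta is simply the increase in whatever values are analysed. That reading is possible, but it confirms that the meaning of the primary outcome depends on the branch. Logging cortisol is not itself an error, and the rule is mechanical and stated in advance.

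A reader might infer two stronger points that the documents do not support:

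- **Inflated false positives in the RCT.** The rule does not let the analyst pick the better scale. Under the null, randomisation makes both scales valid, and the two-stage rule rejected in 4.6–6.3% of simulated trials. The 7.6–8.0% found when the more favourable scale is chosen is not this rule's error rate.
- **A reversed RCT result.** A reversal needs arms that differ in pre-stressor cortisol, or chance. Adjusting for that session's pre-stressor level would largely remove true reversals, although the covariate named in Hypothesis testing, a baseline cortisol response, is not clearly that level.

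The reversal cases concern HR versus LR, which the Background places outside the main RCT. There the cortisol t-tests are unadjusted; the covariate regression is specified only for interpretation bias.

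**Conclusion.** The point holds in a limited form. The primary reactivity estimand is not fixed in advance: a count of Shapiro–Wilk failures on individual swab variables chooses between an absolute rise and a fold change, and only an increase is defined. With strong skew the trial will almost surely test a fold change while describing an increase. With mild skew the branch is uncertain, and for small effects the scales can disagree on significance in roughly 20–30% of trials. That is a disagreement rate between scales, not the probability that the rule changes the verdict.

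Type I error in the RCT and the sample size are unaffected. A change of direction is plausible mainly for H2, if basal levels differ. The size rests on assumed lognormal cortisol, assumed SDs and correlations, a 0.05 test level and, for the 21–32% range, a count of 12 variables. No figure was derived for recovery, so the sizes apply to reactivity only; the scale of recovery is open in the same way. This deserves correction before the cortisol data are seen, but it does not invalidate the design.

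**What to change.** Remove the Shapiro–Wilk switch and fix one scale before data are seen. For example: all cortisol values are analysed as natural logs; reactivity is ln(peak) minus ln(pre-stressor) and is reported as the peak to pre-stressor ratio; recovery is the logged 45-minute value corrected for the logged pre-stressor value; the absolute rise is a named sensitivity analysis. If the absolute rise is the quantity of interest, keep raw values as primary, use bootstrap or permutation inference, and make the ratio the sensitivity analysis. In either case, check the residuals of the analysed indices, by plot, instead of testing the separate swabs.

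The cost is a reworded definition, about two sentences in the analysis section, and one extra analysis. No new data and no change to the sample size are needed.
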